#### Progressive resistive exercise

Previous work has indicated that the tibialis posterior is preferentially recruited during a resisted foot adduction exercise in persons with pes planus [23] and that this muscle is selectively activated when flat-footed subjects perform the exercise while wearing arch supporting orthoses and shoes [24]. Therefore, the exercises will consist of isolated loading (plantar flexion and adduction) of the posterior tibialis musculotendinous unit and will be performed with the subjects wearing both orthoses and shoes. The exercises will be performed using a specialized exercise unit, which can be manipulated to progressively load the tendon either concentrically or eccentrically depending on group assignment (Figure 2). Subjects will begin resistive exercise when custom orthoses are delivered (1–2 weeks after evaluation).

### Intervention group assignment

Subjects will be randomly assigned to one of the three groups: 1) orthoses wear and calf stretching; 2) orthoses wear, calf stretching, and a progressively challenging concentric exercise program; 3) orthoses wear, calf stretching, and a progressively challenging eccentric exercise program.

#### Orthoses (ORTH)

Subjects in the orthoses group will wear custom foot orthoses in athletic shoes for 90% of waking hours. They will be instructed in performing calf stretches as described earlier. A series of six, 30-second stretches on the involved leg will be performed twice daily. Subjects will begin to perform calf stretches on the day of initial evaluation.

#### Orthoses + concentric exercise program (CONC)

Subjects in the concentric exercise group will wear custom foot orthoses and perform calf stretches as described for the orthoses group. They will also be instructed in the performance of the concentric exercise program (consisting of plantar flexion and adduction using a specialized exercise unit). The exercise will be performed slowly (5 seconds thought the range of motion). A series of 3 sets of 15 repetitions will be performed twice daily on the involved side. Between sets, rest periods will be 1–2 minutes. The resistance, provided by a constant force extension spring, will be set at 2 pounds for the first week and progressed to tolerance and ability throughout the 10-week concentric intervention program.

#### Orthoses + eccentric exercise program (ECC)

Subjects in the eccentric exercise group will wear custom foot orthoses and perform calf stretches as described for the orthoses group. They will also be instructed in the performance the eccentric exercise regimen using a specialized exercise unit, which requires plantar flexion and resistance to adduction. The exercise will be performed slowly (5 seconds throughout the range of motion). A series of 3 sets of 15 repetitions will be performed twice daily on the involved side. Between sets, rest periods will be 1–2 minutes. The resistance, provided by a constant force extension spring, will be set at 2 pounds for the first week and progressed to tolerance and ability throughout the 10-week eccentric intervention program.

Subjects will have an Exercise Record Chart where they will record the number of performed stretches and exercises as well as reflections on their performance (ease; if discomfort, then location and intensity). Subjects will meet with an intervention therapist once per week for 10 weeks so that the quality of stretches and motion during the exercise can be assessed and resistance can be added as tolerated or decreased as needed.

### Data analysis

A 3 × 3 ANOVA with repeated measures will identify differences in the FFI across groups (ORTH, CONC, ECC) and between testing sessions (PRE, POST, 6-MONTH FOLLOW UP). All analyses will be performed using SPSS statistical software (SPSS Inc., Chicago, IL). All significance levels will be set at p < 0.05.

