The current study in persons with tibialis posterior tendinopathy was motivated by the significant improvements documented for the eccentric training program for persons with Achilles tendinosis. The greater improvements demonstrated in response to an eccentric compared to a concentric strengthening program suggest that exercise interventions which incorporate an eccentric strengthening component may lead to more successful outcomes than concentric strengthening programs in the treatment of tendinosis. Our study will explore the effectiveness of an eccentric versus concentric strengthening intervention while wearing an orthoses to results obtained while using only an orthoses. There are no controlled studies evaluating the effectiveness of exercise, orthoses, or orthoses and exercise on PTTD. Findings from this research will be invaluable to PTTD intervention programs, as these data will provide critical information that will lead to more efficacious treatment interventions to enhance function and quality of life in persons with posterior tibialis tendon dysfunction.

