### Timing of evaluation

#### Pre-intervention (PRE)

A standard orthopedic lower quadrant assessment documenting structural condition, mobility and strength, will be followed by the administration of the *Foot Functional Index, Physical Activity Scale, and SF-36 questionnaires*, and performance of a *5-Minute Walk Test, 50-Foot Walk Test*, as well as the *Timed Up and Go*. The *Visual Analogue Scale *for pain will be administered after each functional test.

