### Sample size

The selection of 45 subjects for this study (15 subjects per group), is based on clinical observations, attrition rate, and power analysis. Clinical observations have indicated that the inter-subject variability with respect to pain, disability and function is moderate to high. Therefore, all power calculations have taken this increased variability into consideration. A 20% subject attrition rate is anticipated. The possible attrition rate is attributed to length of the rehabilitative program, elimination of symptoms, or increase of symptoms, need for surgery, and prior attrition rate of existing randomized control trials. The *Foot Functional Index *will be used as the primary outcome of this study. The remaining functional, health status, and pain variables will be used as secondary outcome variables. Power calculations were based on an alpha level of 0.05 and beta of 0.8 with respect to the FFI pain score.

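### The planned ANOVA names only the group and session main effects and counts PRE as an outcome, which dilutes the treatment effect; no eccentric-versus-concentric comparison is named

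*Protocol article*

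**What the plan says.** The Data analysis section gives one analysis of the primary outcome: a 3 × 3 repeated-measures ANOVA that "will identify differences in the FFI across groups (ORTH, CONC, ECC) and between testing sessions". The sessions are "PRE, POST, 6-MONTH FOLLOW UP", so the pre-treatment FFI is one of the three outcome levels. On error rates it says "All significance levels will be set at p < 0.05".

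The Background states the question: "Our study will explore the effectiveness of an eccentric versus concentric strengthening intervention while wearing an orthoses", set against orthoses alone. The Abstract says the same.

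The Pre-intervention (PRE) section shows that baseline FFI is already collected from everyone: "A standard orthopedic lower quadrant assessment documenting structural condition, mobility and strength, will be followed by the administration of the" FFI and the other questionnaires.

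Under Sample size: "The selection of 45 subjects for this study (15 subjects per group"), and "A 20% subject attrition rate is anticipated".

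**The concern.** The two differences named are the main effects of the two factors. Neither is the sharpest reading of a randomised treatment effect.

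- **Group main effect.** It averages FFI over all three sessions. Randomisation makes the arms equal in expectation at PRE, so one third of that average cannot carry a treatment difference.
- **Session main effect.** It pools the arms and carries no between-arm information. The Study population section recruits people during a pain episode, so improvement over time can come from natural history or regression to the mean.
- **Eccentric versus concentric.** A three-group omnibus test says that some arms differ, not which ones.

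At stake are sensitivity in a small trial and clarity about what counts as the planned result. As the paragraph stands, a group effect, a session effect or an interaction could each be presented as the planned finding.

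**Working it through.** **The plan's own figure.** The 45 cannot be reproduced, because the article gives no effect size or SD. Only the attrition step can be checked: 12 / 0.8 = 15 per group and 36 / 0.8 = 45. That leaves 12 completers per arm. The article says "Power calculations were based on an alpha level of 0.05 and beta of 0.8 with respect to the FFI pain score". Read literally, a beta of 0.8 is 20% power; presumably 80% power is meant. Nothing below depends on it.

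**Inputs from the article:** n = 12 per arm after attrition, alpha 0.05, three arms, three sessions.

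**Assumptions, not in the article:** SD 1 at each session; compound symmetry with correlation r from 0.3 to 0.8; no group difference at PRE; one arm better by d = 1 SD at both POST and 6 months, the other two equal. For scale, an exact two-sided t-test has 80% power at d = 1.20 with 12 per group and at d = 1.06 with 15.

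**Noncentrality (lambda).** With one arm differing by d, the between-group sum of squares is S = n × d² × 2/3 = 12 × 1 × 2/3 = 8.

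- Group main effect: the effect is (0 + d + d)/3 = 2d/3 and the variance of a subject's three-session mean is (1 + 2r)/3. So lambda = S × (4/9) / ((1 + 2r)/3), F on 2 and 33 df.
- Group × session: lambda = S × (2/3) / (1 − r), F on 4 and 66 df.
- Baseline-adjusted mean of POST and 6 months: the residual variance is (1 + r)/2 − r². So lambda = S / ((1 + r)/2 − r²), F on 2 and 32 df.

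At r = 0.5 these are 8 × 0.444 / 0.667 = 5.33; 8 × 0.667 / 0.5 = 10.67; and 8 / (0.75 − 0.25) = 16.00.

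| r | Group main: lambda, power | Group × session: lambda, power | Baseline-adjusted mean: lambda, power |
|---|---|---|---|
| 0.3 | 6.67, 0.59 | 7.62, 0.55 | 14.29, 0.91 |
| 0.5 | 5.33, 0.49 | 10.67, 0.71 | 16.00, 0.94 |
| 0.7 | 4.44, 0.42 | 17.78, 0.92 | 22.22, 0.99 |
| 0.8 | 4.10, 0.39 | 26.67, 0.99 | 30.77, 1.00 |

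Simulation (5000 runs, d = 1, 12 per group) agreed with the group and interaction formulas to within about 1 point.

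**Share of information.** As ratios of lambda, the group main effect keeps 47% / 33% / 20% / 13% of the information in the baseline-adjusted comparison at r = 0.3 / 0.5 / 0.7 / 0.8. Against the interaction it keeps 88% / 50% / 25% / 15%, but the interaction spends 4 numerator df. That is why the interaction is slightly behind in power at r = 0.3.

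**Sensitivity to effect size.** Over r = 0.3 to 0.8, the relative loss of power for the group main effect against the baseline-adjusted comparison is 49–80% at d = 0.6, 35–61% at d = 1.0 and 23–47% at d = 1.2. Against the interaction, the loss over the same range of settings runs from none to 75%.

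**Eccentric versus concentric.** S is the same whether ECC is the one arm that differs or ORTH is. If CONC and ECC are equal and both 1 SD better than ORTH, the interaction test at r = 0.5 is still significant 71% of the time, with no ECC–CONC difference. A contrast is needed. From the baseline-adjusted mean, the ECC-versus-CONC contrast has power 0.89 / 0.92 / 0.98 at r = 0.3 / 0.5 / 0.7 if the two differ by 1 SD, but 0.36 / 0.39 / 0.51 if they differ by 0.5 SD.

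**The case against.** The strongest reply is that the sentence can be read as listing the two factors and their levels. A 3 × 3 repeated-measures ANOVA contains the group × session term, and SPSS reports it by default. Pairwise follow-up is commonly left to the full protocol or analysis plan, which is not shown. Much of this stands, and it rules out three stronger readings that a reader might infer.

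- *That neither named effect tests the randomised comparison.* The arms are randomised, so the group main effect is a valid test of it, only diluted.
- *That eccentric versus concentric is never tested.* Both are levels of the group factor, and silence on contrasts does not mean that none will be made. The article supports only the statement that no such comparison is named.
- *That most of the power is lost.* This depends on an effect size and a correlation that the article does not give. At r = 0.3 the group main effect is slightly better than the interaction (0.59 against 0.55).

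Nor does the article say that a session effect will be reported as effectiveness; the wording merely leaves room for it. Using PRE as a covariate rather than a repeated level is a gain in efficiency, not the repair of an invalid test.

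What remains is that the article does not just omit detail. It states which differences the analysis will identify, and these are not matched to the question in its own Background.

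**Conclusion.** The point holds in a limited form. The Data analysis paragraph names two main effects with PRE as an outcome. The group effect is valid but shows 2/3 of a lasting difference, the session effect is a before-after change without a control, and the central comparison is not named.

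Against the baseline-adjusted comparison, the group main effect is weaker at every effect size and correlation examined; with a 1 SD effect and r from 0.3 to 0.7, power is 0.42–0.59 against 0.91–0.99. Against the interaction, the result depends on r. These figures rest on 12 completers per arm, compound symmetry and an equal effect at POST and 6 months. Only the completer count follows from the article. The dilution to 2/3 needs no SD or correlation, only no expected difference at PRE and an equal effect at both later sessions.

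**What to change.** Reword the first sentence of Data analysis along these lines: FFI at POST and 6 months will be analysed in a linear mixed model (in SPSS) with group, session and group × session, and with PRE FFI as a covariate; the treatment effect is the baseline-adjusted group comparison; the ECC-versus-CONC and exercise-versus-ORTH contrasts are stated in advance; the session main effect is descriptive only.

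If the 3 × 3 ANOVA is kept, name group × session as the treatment test and state the same contrasts. This makes the treatment test clear, but under the assumptions above it gains power over the group main effect at r = 0.5 and above, not at r = 0.3.

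No fixed testing order should be imposed. Putting ECC versus CONC first would block a formal claim for exercise over orthoses whenever the two exercise arms work equally well.

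The cost is one reworded paragraph and one degree of freedom for baseline, with the same data and software. The change does not rescue a small ECC–CONC difference: at 0.5 SD the contrast has power of only 0.36 to 0.51 for r = 0.3 to 0.7.

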### Sample size

The selection of 45 subjects for this study (15 subjects per group), is based on clinical observations, attrition rate, and power analysis. Clinical observations have indicated that the inter-subject variability with respect to pain, disability and function is moderate to high. Therefore, all power calculations have taken this increased variability into consideration. A 20% subject attrition rate is anticipated. The possible attrition rate is attributed to length of the rehabilitative program, elimination of symptoms, or increase of symptoms, need for surgery, and prior attrition rate of existing randomized control trials. The *Foot Functional Index *will be used as the primary outcome of this study. The remaining functional, health status, and pain variables will be used as secondary outcome variables. Power calculations were based on an alpha level of 0.05 and beta of 0.8 with respect to the FFI pain score.

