#### 6-Month follow up (6-MONTH FOLLOW UP)

Six months after the completion of the intervention, subjects will be asked to complete the *Foot Functional Index, the Physical Activity Scale, SF-36 questionnaire, and the Global Rating Scale*. A pre-addressed, stamped envelope will be included in the correspondence. Patients will also be contacted via phone to ensure a timely response.

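### The planned repeated-measures ANOVA in its classical form keeps only subjects with all three FFI scores, although the article expects partly outcome-related attrition; this puts the primary comparison at risk of bias if that loss differs between arms

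*Protocol article*

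**What the plan says.** Under Data analysis, the Protocol article fixes the primary method: "A 3 × 3 ANOVA with repeated measures will identify differences in the FFI across groups". The sessions are PRE, POST and the 6-month follow-up. On software it says "All analyses will be performed using SPSS statistical software" and names no procedure within that package.

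Under Sample size, it plans 45 subjects (15 per group), makes the FFI the primary outcome and anticipates 20% attrition. The reasons given are these: "The possible attrition rate is attributed to length of the rehabilitative program, elimination of symptoms, or increase of symptoms, need for surgery". Attrition in earlier randomised trials is a further basis. The 20% is not split by reason, arm or time, and attrition is used only to support the choice of 45.

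On data collection, POST is a re-evaluation with the same tests as at baseline. At 6 months the FFI goes out by post: "A pre-addressed, stamped envelope will be included in the correspondence. Patients will also be contacted via phone to ensure a timely response".

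**The concern.** A classical repeated-measures ANOVA needs a complete row for each subject. In the standard SPSS general linear model procedure, a subject missing one session is removed altogether, with the scores already collected. The FFI measures pain, function and activity level, so symptoms resolving, symptoms worsening and surgery are closely tied to the primary outcome. The article thus pairs a completers-only method with a forecast that some subjects will be incomplete because of how they responded.

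A larger sample replaces lost numbers, not the particular people lost. If good responders tend to leave one arm and poor responders another, the remaining subjects are no longer comparable as randomised. A real effect can be diluted, or an apparent one can arise. An effective treatment could itself produce such a difference: if subjects in every arm leave once symptoms pass the same absolute level of resolved or worse, the arms lose different people.

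**Working it through.** **Numbers retained.** 45 × (1 − 0.20) = 36, or 12 per group. Conversely, 36 / 0.80 = 45, so the planned size is consistent with allowing for 20% loss. The power calculation itself cannot be reproduced, because no SD or effect size is given.

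**Assumptions for the bias (none is in the article).** ECC versus ORTH; SD 1 at each session; correlation 0.6 between every pair of sessions; everyone attends POST, and loss afterwards depends on the POST score. Differences are signed so that positive favours ECC.

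**Opposite tails: ORTH loses its worst 20%, ECC its best 20%.**

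- Cutting 20% from one tail of a normal distribution moves the mean of the rest by φ(0.842)/0.80 = 0.280/0.80 = 0.35 SD.
- The two arms move towards each other, so the POST difference loses 2 × 0.35 = 0.70 SD.
- Through the correlation, the PRE and 6-month differences each lose 0.6 × 0.70 = 0.42 SD.

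With a true effect of 1.0 SD at POST and 6 months, and none at PRE:

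| Completers' contrast | Calculation | Result (SD) |
|---|---|---|
| PRE level | 0 − 0.42 | −0.42 |
| POST level | 1.00 − 0.70 | 0.30 |
| 6-month level | 1.00 − 0.42 | 0.58 |
| PRE–POST change | 0.30 − (−0.42) | 0.72 |
| PRE–6-month change | 0.58 − (−0.42) | 1.00 |

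With no true effect, the same pattern gives a spurious 0.42 − 0.70 = −0.28 SD in PRE–POST change and −0.42 SD in 6-month level.

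The 6-month change contrast escapes only because the correlations are equal. In general its bias is 0.70 × (POST–6-month correlation minus PRE–POST correlation).

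**Same tails of each arm's own distribution, or random loss.** Both arms shift equally, so every contrast is unchanged and the bias is zero.

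**Same absolute cut-offs in both arms.** Take a true effect of 0.8 SD, POST means of −0.5 (ORTH) and −1.3 (ECC), and loss below −2.3 or above 0.6.

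- Loss is about 17% in ORTH and 19% in ECC.
- The mean of those kept shifts by (0.0790 − 0.2179)/0.828 = −0.168 in ORTH and (0.2420 − 0.0656)/0.813 = +0.217 in ECC, a gap of 0.385.
- PRE–POST change: 0.80 − 0.4 × 0.385 = 0.65 SD.
- 6-month level: 0.80 − 0.6 × 0.385 = 0.57 SD.
- With no true effect, the arms are cut alike and there is no bias.

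Simulation with 300,000 subjects per arm agrees with these results.

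**What a mixed model repairs.** In the opposite-tail case with a 1.0 SD effect, a likelihood model using all scores returns 1.00 SD at both sessions, because loss depends on a POST score that is on file. If the same subjects miss POST as well, only PRE informs the model:

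- Among those kept, POST variance is 1 − 0.842 × 0.35 − 0.35² = 0.583.
- PRE variance is 1 − 0.36 × (1 − 0.583) = 0.850.
- The slope of POST on PRE is 0.6 × 0.583/0.850 = 0.41.
- The slope of 6 months on PRE is (0.6 − 0.36 × 0.417)/0.850 = 0.53.
- Estimated effects are 0.30 + 0.42 × 0.41 = 0.47 SD at POST and 0.58 + 0.42 × 0.53 = 0.80 SD at 6 months.

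This improves on 0.30 and 0.58 but is not full recovery.

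**The case against.** The strongest reply is that bias has not been demonstrated, and that is right. The article says nothing about loss by arm, and loss of the same form within each arm leaves the contrast intact. A reader might infer from the list of reasons that the primary comparison is biased, or that those excluded are simply the best and worst responders. The text supports neither: programme length and earlier trials' attrition are listed too, with no split.

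Other limits also stand:

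- With PRE as a session, the treatment effect would normally be tested by the group × session interaction, which concerns change. The 0.30 and 0.58 SD level differences overstate the damage to that test; 0.72 and 1.00 SD are the relevant values. The level bias enters the group main effect.
- A reader might suppose that 20% miss POST and another 20% independently miss 6 months, leaving 45 × 0.8 × 0.8 ≈ 29. The article states 20% subject attrition, which gives 36.
- A reader might infer that stopping treatment ends follow-up. The article does not say so. Its 6-month mailing excludes nobody, and neither does its POST evaluation, although it describes no mail route for POST.
- Deletion of incomplete subjects follows from the classical method; the article does not state it.

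It can also be said that missing-data handling belongs in a fuller document. That covers silence about analysis sets or imputation. It does not cover a named method that sits poorly with dropout reasons stated in the same article.

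**Conclusion.** The point holds as a risk. The named primary analysis, in its classical form, would discard about 9 of 45 subjects at the stated 20% attrition, some of them expected to leave for reasons tied to the FFI. Whether this biases the comparison depends on whether such loss differs between arms, which the article does not tell us.

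Under the assumed patterns, bias in PRE–POST change runs from zero to about 0.28 SD. Bias in PRE–6-month change is zero when the correlations are equal, and level differences lose up to 0.70 SD at POST and 0.42 SD at 6 months. All of these rest on assumed correlations, effect sizes and dropout rules. For scale, 12 per arm detects a pairwise difference of about 2.80 × √(2/12) = 1.14 SD with 80% power at two-sided 0.05, so there is little room for dilution.

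This is a worthwhile, inexpensive improvement of moderate importance. It is not a flaw that invalidates the trial.

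**What to change.** Replace the primary analysis with a likelihood-based mixed model for repeated measures, for example the MIXED procedure in SPSS, fitted to all randomised subjects as assigned and using every available FFI score. The group × session contrasts remain the question.

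Extend the mail and telephone route already planned for 6 months to the POST FFI for subjects who do not attend, including those who have stopped the programme. This matters because the model alone does not fully correct loss before POST, and scores not collected then cannot be recovered later.

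Add one sensitivity analysis for outcome-related missingness, for instance assigning an unfavourable FFI to subjects lost through worsening or surgery.

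The cost is a change of analysis wording and, at 20% attrition, up to about 45 × 0.20 = 9 extra POST questionnaires. The small downside is that some scores will have been collected after the programme was stopped. The software and sample size need not change.
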